## Abstract

Background: Many stroke survivors suffer from sensorimotor deficits, especially balance impairments. The purpose of this trial is to investigate whether the designed Immersive Virtual Reality training program is better in the short term (15 sessions) and in the medium term (30 sessions) than physiotherapy training with Bayouk, Boucher and Leroux exercises, with respect to static balance in sitting and standing, dynamic balance and quality of life in patients with balance impairment in stroke survivors. Methods: This study is a randomized controlled trial with two treatment arms and evaluators blinded, and a functionality treatment group in combination with specific balance exercise training according to Bayouk, Boucher and Leroux (control group) or a balanced treatment using Immersive VR. The primary outcome will be static, Dynamic balance and gait measured by Bestest Assessment Score (BESTest), Berg Scale (BBS), Pass Scale (PASS) and Time Up and Go test (TUG). The secondary outcome will be the stroke-associated quality of life using the Stroke Quality of Life Scale (ECVI-38). Conclusions: The results of this study may add new insights into how to address balance using Immersive Virtual Reality after a stroke. If the new training approach proves effective, the results may provide insight into how to design more comprehensive protocols in the future for people with balance impairments after stroke.

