This study aims to determine whether the designed Immersive VR training program is better in the short term (15 sessions) and medium term (30 sessions) than physiotherapy training with exercises by Bayouk, Boucher and Leroux [39] regarding the change of measures related to static sitting, and standing balance and dynamic balance in post-stroke patients.

Secondary objectives verify the impact on quality of life and safety of the application of this type of technology.

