### 2.11. Data Management and Statistical Analysis

Sample size: For instance, to achieve 80% power to detect differences in contrast to the null hypothesis H₀, mean difference in BESTest is equal to the limit of superiority, using a one-sided Student’s t-Test (superiority) for two independent samples, taking into account that the significance level is 5%, and assuming that the superiority limit is 7.81 units, as suggested in the article by Candance, et al., [55]. Additionally, the proportion of patients in the control group with respect to the total is 50%; it will be necessary to include 18 patients in the control group and 18 in the experimental group, a total of 36 patients in this study. Considering that the expected percentage of dropouts is 20%, it would be necessary to recruit 22 patients in the control group and 22 patients in the experimental group, a total of 44 patients in this study.

Patient characteristics and comparisons at baseline: To assess the comparability of the two groups, the characteristics of the patients assigned to each group will be presented in a table. Discrete variables will be summarized as frequencies and percentages. Continuous variables and time intervals will be summarized using means, standard deviation, or median and interquartile range. Both groups need to be homogeneous at baseline.

The statistical analysis will be carried out by an intention-to-treat analysis.

Analysis of the main objectives: Normality tests of the dependent variables were undertaken using the Kolmogorov–Smirnov test. The description of the results of the dependent variables was also performed, using either the mean and the standard deviation or the median and interquartile range, depending on the adjustment of these variables to normality. 

To respond to the main objective, with each primary result, hypothesis tests will be performed (where the alternative hypothesis is the greater efficacy of the experimental treatment compared to the conventional one), and estimates will be provided by 95% confidence intervals. In addition, the t-Student test will be used for independent samples in the parametric case and the Mann–Whitney U test for the non-parametric case.

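### Each primary scale gets its own directional test and the aim covers two visits, but no lead outcome, lead visit or rule for overall success is named, so the error rate of the superiority claim is not fixed

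*Protocol article*

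**What the plan says.** - **Aim (Introduction).** The question is whether the VR programme is "better in the short term (15 sessions) and medium term (30 sessions") than the comparator exercises, for static and dynamic balance. Neither visit is ranked above the other.
- **Primary outcomes.** The Abstract names "Bestest Assessment Score (BESTest), Berg Scale (BBS), Pass Scale (PASS) and Time Up and Go test (TUG"). Table 3 names PASS, BESTest, the 10 m walk test and TUG, without BBS. Section 2.7 describes all five measures. Table 3 schedules its primary scales at both post-baseline visits.
- **Main analysis (2.11).** For the main aim, the plan is that "with each primary result, hypothesis tests will be performed". These tests are directional: their alternative is that the VR arm does better than the control arm. The same paragraph promises 95% intervals for the estimates. It gives no significance level and does not say whether the intervals are one- or two-sided.
- **Sample size (2.11).** The calculation is for BESTest with a one-sided t-test, "taking into account that the significance level is 5"%, and 80% power, giving 18 evaluable patients per arm. It offers BESTest as an example and names no visit.

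**The concern.** The plan commits to several directional tests for one objective and leaves open which of them decides it. With four scales at two visits there are 8 chances to find a favourable result, or 10 if all five measures count. The scale and visit to headline could then be chosen after the results are known, and the 5% used to plan the trial would not describe the error rate of its main conclusion. The Discussion expects the findings to change how stroke patients are treated, so the basis for the claim should be settled beforehand. Because the two primary lists differ, even the set of tests is not defined.

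**Working it through.** **The plan's own figure.** No SD is given, so 18 per arm cannot be checked directly, only solved backwards. The normal approximation is n per arm = 2 × ((z₀.₉₅ + z₀.₈₀)/d)². With 1.645 + 0.842 = 2.486 and n = 18, d = 2.486/√9 = 0.829. Treating 7.81 as the difference to be detected, the implied SD is 7.81/0.829 ≈ 9.4 (about 9.2 with the t distribution). This covers one scale, tested once, at one-sided 5%.

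**Number of tests.** Either explicit list: 4 scales × 2 visits = 8. All five measures in section 2.7: 5 × 2 = 10.

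**Per-test level.** One-sided 5% if the sample-size level carries over to the analysis. One-sided 2.5% if decisions follow two-sided 95% intervals. The text supports neither reading conclusively, so both are shown.

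**Chance of at least one false positive** when there is no true difference on any scale at either visit, and any single positive test counts:

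- Independent tests: 1 − (1 − α)^k. For example, 1 − 0.95⁸ = 0.337 and 1 − 0.975⁸ = 0.183.
- Equal pairwise correlation ρ: 1 − ∫ Φ((c − √ρ·u)/√(1 − ρ))^k φ(u) du, with c = 1.645 (5%) or 1.960 (2.5%).

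The documents give no correlations, so those below are assumptions.

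| Tests | One-sided level | Independent | ρ = 0.5 | ρ = 0.7 | ρ = 0.8 | ρ = 0.9 |
|---|---|---|---|---|---|---|
| 8 | 5% | 33.7% | 21.9% | 16.8% | 14.1% | 10.9% |
| 10 | 5% | 40.1% | 24.7% | 18.5% | 15.2% | 11.5% |
| 8 | 2.5% | 18.3% | 12.5% | 9.5% | 7.9% | 6.0% |
| 10 | 2.5% | 22.4% | 14.4% | 10.7% | 8.6% | 6.4% |

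A simulation with separate correlations between scales (0.5 to 0.8) and between visits (0.5 to 0.9) gives similar results. At one-sided 5% it gives 13.9% to 23.8% for four scales and 15.3% to 27.3% for five. At one-sided 2.5% it gives 7.8% to 13.5% and 8.7% to 15.8%.

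**Cost of splitting alpha instead of ordering the tests.** Bonferroni over 8 tests gives 0.05/8 = 0.00625, critical value 2.498. At 18 per arm and d = 0.829, power for BESTest is Φ(0.829 × √9 − 2.498) = Φ(−0.011) ≈ 50%, down from 80%. Restoring 80% needs 2 × ((2.498 + 0.842)/0.829)² ≈ 32.5, so 33 evaluable patients per arm. Over 10 tests (level 0.005), power is about 46% and 35 per arm are needed.

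**The case against.** A reader might infer that every scale is tested at one-sided 5% and that the false-positive risk is therefore several times 5%. The documents do not support putting it that firmly, for four reasons.

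1. **Level.** One-sided 5% appears only in the sample-size sentence. The analysis paragraph gives a direction and 95% intervals. At one-sided 2.5% per test and high correlation, the overall rate is only slightly above 5%. This objection stands, and the range must cover both levels.
2. **Success rule.** The aim joins 15 and 30 sessions, and static and dynamic balance, with the word and. If all tests had to succeed, there would be no inflation. The text does not state that rule, and only BESTest has a sample size, so power for joint success is not addressed. The objection turns the point into an undefined rule; it does not remove it.
3. **Size.** Independence is implausible for overlapping balance measures taken twice in the same patients, so 34% and 40% are outer limits. The count of 10 matches neither explicit primary list and is the upper case.
4. **Detail held elsewhere.** A condensed article may leave multiplicity adjustment to a fuller document, so its absence is not itself a fault. But this article itself commits to a separate test of each primary result, without a lead, on lists that disagree.

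It is also tempting to say that the sample size already makes BESTest at 30 sessions the primary endpoint. It does not: the calculation names no visit and presents BESTest only as an example.

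**Conclusion.** The point holds in this form: the plan fixes separate directional tests over four scales (five measures in all) and two visits without naming a lead outcome, a lead visit or a rule for overall success. The size depends on three things that the documents leave open: the success rule, the per-test level and the correlations. If any single success suffices, the overall false-positive chance over 8 tests is about 11% to 22% at one-sided 5%, or about 6% to 13% at one-sided 2.5%. Over 10 tests it is about 12% to 25%, or 6% to 14%. Those ranges assume correlations from 0.9 down to 0.5. That the inflation will occur is not established. What is established is that the plan does not prevent it and leaves the choice of headline result open.

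**What to change.** 1. Make the primary lists in the Abstract, section 2.7 and Table 3 agree.
2. Name one lead outcome at one visit. BESTest is the natural candidate because it is the only scale with a sample size. The visit, for example 30 sessions, is for the sponsor to fix before any unblinded data are seen.
3. Test that endpoint first at the full stated alpha. Only if it succeeds, test the other visit and the remaining scales in a fixed sequence or with Holm adjustment. Alternatively, report them as estimates with intervals and no superiority claim.
4. If testing continues beyond the lead, keep a dynamic-balance measure such as TUG in the sequence. Section 2.7 and Table 3 class BESTest under static balance and functional mobility, and dynamic balance is part of the main aim.
5. State one alpha and sidedness for the analysis, and intervals that match.

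Cost: wording in the Abstract, Introduction, 2.7, 2.11 and Table 3, and no added patients. The other scales lose stand-alone confirmatory status. The aim must be reworded to match; with BESTest as lead, dynamic balance would have no primary measure of its own under the document's own classification.

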### 2.4. Intervention Protocol/Procedure

Eligible subjects will be identified by the stroke diagnosis; they will be patients admitted to the Neurology Service of the Miguel Servet Hospital in Zaragoza. In an initial visit, the nursing staff will inform those potentially eligible, who will be pre-selected based on whether or not they meet the inclusion and exclusion criteria for this study. Likewise, they will proceed to explain this study to the included subjects, collect the willingness to participate and provide the informed consent document.

Prior to random assignment, two physiotherapists who are experts in neurological assessment will evaluate the outcome variables for each participant. Subsequently, patients will be randomly assigned to the control group or the experimental group in a 1:1 ratio, computerized random assignment program. The patient will be informed that in subsequent evaluations, they do not reveal to the evaluators to which group they have been assigned.

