### 2.7. Outcomes

All study participants will be evaluated before starting treatment (baseline) at 15 sessions and 30 sessions. The outcome measures are compiled in Table 3. 

The parameters of balance in sitting and standing static and dynamic and in the temporospatial and kinematic parameters of gait will be obtained from the following tests and scales. 

For static balance and functional mobility, the PASS Spanish version [21,45], the BBS [34] and the BESTtest [46] have been used. 

BBS has a high relative reliability with interrater reliability estimated at 0.97 (95% CI 0.96 to 0.98) and intra-rater reliability estimated at 0.98 (95% CI 0.97 to 0.99). The absolute reliability of the BBS varies across the scale, with minimal detectable change with 95% confidence varying between 2.8/56 and 6.6/56 [41].

PASS is a 12 items performance-based scale used for assessing and monitoring postural control following a stroke. It consists of a 4-point scale where three items are scored from 0 to 3, and the total scoring ranges from 0 to 36 [45]. The minimal detectable change in subacute stroke is 2.22 points [47]; in acute stroke, 1.8 points [48]; and in chronic stroke, it is 3.2 points [49].

BESTest consists of 27 tasks, with 36 items in total. Each item is scored based on ordinal scale scoring from 0 to 3, where 3 represents best performances, and 0 represents worst performances. Scores for the total test are provided as a percentage of total points [50]. Additionally, the minimal detectable change in subacute stroke is 7.81 points [50]. 

To measure dynamic balance and gait, the TUG test [51] and the 10 m walk test [52] will be used. 

In the TUG test, the patient rises from a chair, walks three meters in a straight line, turns, returns and sits down while the examiner times the time required to perform the test. In addition, the TUG assesses the risk of falling. A score of less than 10 s indicates a low risk of falling, between 10 and 20 s indicates frailty with a higher risk of falling, and more than 20 s a high risk of falling [51]. The minimum detectable change in stroke is estimated at 2.9 s [53].

10 m walk test has an excellent interrater reliability estimated ICC = 0.87 to 0.88, and an excellent interrater reliability ICC = 0.998. The minimum detectable change is set at 0.05m/s, and a substantial change is set at 0.10m/s [52].

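### The primary comparison names no baseline covariate and appears to be chosen by a Kolmogorov–Smirnov screen: it is a valid test, but it gives up precision and leaves the tested quantity open

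*Protocol article*

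**What the plan says.** The baseline values exist. Section 2.4 states: "Prior to random assignment, two physiotherapists who are experts in neurological assessment will evaluate the outcome variables for each participant". Section 2.7 adds: "All study participants will be evaluated before starting treatment (baseline) at 15 sessions and 30 sessions". Table 3 marks PASS, BESTest, the 10 m walk test and TUG at T0, T1 and T2.

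On the main objectives, section 2.11 reports that "Normality tests of the dependent variables were undertaken using the Kolmogorov–Smirnov test". It then names the between-group tests: "the t-Student test will be used for independent samples in the parametric case" and "the Mann–Whitney U test for the non-parametric case". It also promises 95% confidence intervals. No covariate, ANCOVA or repeated-measures model appears for these outcomes. Baseline enters only through a comparability table and the sentence "Both groups need to be homogeneous at baseline".

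The aim in section 1 is worded "regarding the change of measures related to static sitting, and standing balance and dynamic balance in post-stroke patients", but section 2.11 does not say whether final or change scores are compared.

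**The concern.** Three things are fixed badly in the same paragraph.

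- **No baseline covariate.** Entry requires only 30 s of unaided sitting (section 2.2), and section 2.6 describes progression from sitting to ambulation. Baseline scores will therefore vary widely and should predict follow-up scores. Leaving out a predictive covariate that is already measured costs precision, which matters with 36 evaluable patients.
- **Score type unstated.** Final and change scores have different variances, so the efficiency of the planned test cannot be read from the text.
- **Method apparently chosen by a normality screen.** If K-S decides between t and U, the target can be a mean difference for one primary outcome and a rank comparison for another. Section 2.11 names no estimator for the promised interval in the U branch. Uncorrected K-S is also a poor detector of skew at this sample size.

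**Working it through.** **Inputs.** From section 2.11: one-sided alpha 5%, power 80%, 7.81 BESTest units, 1:1 allocation, 18 per arm. Assumed, because the document does not give them: the SD, and the correlation r between baseline and follow-up score. SDs at baseline and follow-up are taken as equal.

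**1. The plan's own sample size.** It cannot be reproduced, because no SD is stated, so I solved backwards. For a two-sample t-test with n = 18 per arm, the noncentrality is d × √(18/2) = 3d, on 34 df with one-sided critical value 1.691. Power of 80% needs 3d = 2.537, so d = 0.846. If 7.81 is the difference to detect, SD = 7.81 / 0.846 = 9.23.

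**2. ANCOVA if final scores would have been tested.** Residual variance is SD² × (1 − r²), so noncentrality is 2.537 / √(1 − r²) on 33 df. The unadjusted test has 80% power.

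| r | Residual variance ratio | Noncentrality | Power |
|---|---|---|---|
| 0.3 | 0.91 | 2.66 | 83% |
| 0.5 | 0.75 | 2.93 | 89% |
| 0.6 | 0.64 | 3.17 | 93% |
| 0.7 | 0.51 | 3.55 | 97% |

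**3. ANCOVA if change scores would have been tested.** The 9.23 is now the SD of change. With σ the SD of a single score, change has variance 2σ²(1 − r) and the ANCOVA residual has σ²(1 − r²). The ratio is (1 + r)/2, and noncentrality is 2.537 / √((1 + r)/2) on 33 df.

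| r | Variance ratio | Noncentrality | Power |
|---|---|---|---|
| 0.3 | 0.65 | 3.15 | 92% |
| 0.5 | 0.75 | 2.93 | 89% |
| 0.6 | 0.80 | 2.84 | 87% |
| 0.7 | 0.85 | 2.75 | 85% |
| 0.9 | 0.95 | 2.60 | 82% |

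The gain grows with r on the first reading and shrinks with r on the second.

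**4. The normality screen (simulated, n = 18).** Uncorrected K-S with estimated mean and SD rejects about 1% of lognormal samples with sigma 0.5, 7% with sigma 0.8 and 3% of exponential samples. With a Lilliefors correction, which the document does not name, rejection is 17% (gamma, skewness 1), 31% (lognormal, sigma 0.5), 53% (exponential) and 74% (lognormal, sigma 1).

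**5. Validity of the two-stage procedure.** Simulating K-S followed by t or U at 18 per arm over a range of shapes gave one-sided type I error of 4.7% to 5.5%.

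**The case against.** - **Baseline may already be used.** The aim speaks of change, and section 2.7 introduces 7.81 as a minimal detectable change. A t-test on change scores does use baseline. A reader might infer from section 2.11 that the test ignores baseline altogether, but the text does not establish that. What stands is that the score type is unstated and no covariate is named. ANCOVA is at least as efficient on either reading, apart from one degree of freedom.
- **The unadjusted test is not wrong.** A reader might infer that chance imbalance biases the estimate, or that the pre-test inflates false positives. Neither follows. Under randomisation the unadjusted comparison is unbiased and its standard error already covers chance imbalance, and the simulated type I error stays near 5%.
- **K-S is not powerless on every reading.** The low rejection rates apply to uncorrected K-S at 18 per arm. With Lilliefors, or with the arms pooled, it does better. The two complaints about the screen also partly offset each other: if it seldom rejects, the target seldom switches; if it is corrected, switching becomes more common.
- **The link from K-S to the choice of test is inferred.** Section 2.11 explicitly ties normality only to the choice of descriptive summary. That it also selects t or U is the natural reading, but it is not stated.
- **ANCOVA is not directly available for every outcome.** Patients who can only sit may have no baseline TUG or walk time. This stands, and the remedy must deal with it.

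**Conclusion.** The point holds as a low-cost improvement, not as an error that invalidates the trial. Section 2.11 commits to an unadjusted two-group comparison, leaves open whether final or change scores are tested, and lets the target differ between outcomes, while the pre-randomisation scores that would sharpen the comparison are already collected.

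The size depends on what the document leaves open. The 0.85 SD is back-solved, not the trial's own figure; section 2.11 in fact calls 7.81 the superiority limit under the null hypothesis. The correlations are assumptions. Over r = 0.3 to 0.7 the gain at 18 per arm is 3 to 17 percentage points on final scores and 12 down to 5 points on change scores, reaching 2 points at r = 0.9. Quoting only the final-score range would overstate what is known.

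Because the protocol itself names the tests, this is not simply a detail left to an analysis plan: one that followed section 2.11 would carry the same choice forward.

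**What to change.** In section 2.11:

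1. **Scales.** Replace the K-S-dependent choice with a pre-specified ANCOVA of the follow-up score on treatment and baseline score, or one mixed model over the 15- and 30-session scores with baseline as covariate. Report the adjusted mean difference with its 95% CI for BESTest and PASS, and for BBS if it stays primary (the abstract lists it, Table 3 does not). This also removes the doubt over final versus change scores, since the adjusted treatment difference is the same for both.
2. **Timed tests.** For TUG and the 10 m walk, fix in advance one method that keeps patients without a baseline time, such as a rank-based analysis that gives the worst rank to those unable to perform the test and adjusts for baseline rank.
3. **Sensitivity.** Keep a rank-based analysis of the scales as a fixed sensitivity analysis, not one triggered by a normality test.

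The cost is one degree of freedom (at r = 0, power falls by less than 0.1 percentage point) and some redrafting. No new data, visits or patients are needed.

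### The tests named for the primary scales use one value per patient, so as stated the 30-session comparison makes no use of the 15-session score, even for patients lost after session 15

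*Protocol article*

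**What the plan says.** The Introduction sets the aim of showing that the VR programme is "better in the short term (15 sessions) and medium term (30 sessions) than physiotherapy training". Section 2.7 gives the assessment times: "All study participants will be evaluated before starting treatment (baseline) at 15 sessions and 30 sessions". Table 3 marks each primary scale it lists at all three times.

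For the primary results, section 2.11 names two tests only: "the t-Student test will be used for independent samples in the parametric case" and "the Mann–Whitney U test for the non-parametric case". It names no repeated-measures model and no baseline adjustment. The same section states: "The statistical analysis will be carried out by an intention-to-treat analysis".

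On dropout, the sample-size paragraph says "Considering that the expected percentage of dropouts is 20" per cent. It raises 18 per arm (36) to 22 per arm (44). Beyond that, section 2.11 says only that reasons for dropout will be explored qualitatively.

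**The concern.** A t-test or Mann–Whitney test compares one number per patient between two groups. With two follow-up visits in the objective, it has to be run once per visit. The 30-session run then has no place for what was observed at 15 sessions. That score predicts the missing 30-session score of a patient who leaves in between, and it has already been collected.

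The medium-term result is the one at stake. If VR patients who are doing poorly tend to leave while control losses are unrelated to progress, the remaining VR patients look better than the randomised group would have. Losses that differ by arm are plausible here: participants are not blinded (section 2.9), treatment-related adverse effects are an outcome (section 2.7), and the Discussion expects immersion to improve adherence. None of this shows that such dropout will occur.

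**Working it through.** **Inputs from the article.** 18 per arm to be analysed, 22 per arm recruited, 20% dropout, one-sided 5% level, 80% power, BESTest limit 7.81 (all section 2.11).

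**The plan's own figure.** 18 × 1.20 = 21.6, rounded up to 22 per arm, 44 in total. Dividing instead gives 18/0.80 = 22.5, so 23 per arm, or 36/0.80 = 45 in total. The stated 44 is reproduced within two patients. Expected completers are 44 × 0.80 = 35.2. About 44 × 0.20 = 8.8 patients, roughly four per arm, could therefore lack a 30-session score.

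**Inputs that must be assumed.**
- *SD.* The article gives none. If 7.81 is read as the difference to be detected, the normal formula gives SD = 7.81 / [(1.645 + 0.842) × √(2/18)] = 7.81 / 0.829 = 9.42. The exact t-test gives 8.97 to 9.23. I use 9.2.
- *Correlation of the 15- and 30-session scores.* Not stated; 0.5 to 0.8 is used.
- *Timing of losses.* Not stated; the main case puts all four per arm after session 15.
- *Dropout rule.* Main case: in the VR arm the log-odds of loss rise by 1 for each SD by which the 15-session score is lower; control losses are random. There is no true effect.

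**Mechanism.** If loss depends only on the 15-session score, then

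bias at 30 sessions ≈ correlation × shift in the mean 15-session score of VR completers.

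Simulation at correlation 0.8 gives a bias of about +1.2, so the shift is 1.2/0.8 = 1.5 points. The bias should then be 0.6 × 1.5 = 0.9 at correlation 0.6 and 0.5 × 1.5 = 0.75 at 0.5. Simulation agrees.

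**Completers' 30-session comparison, simulated (22 per arm, SD 9.2, no true effect).**

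| Scenario | Correlation | Bias (points) | One-sided type I error |
|---|---|---|---|
| Main case | 0.8 | about +1.2 | 10 to 12% |
| Main case | 0.6 | about +0.9 | 9% |
| Main case | 0.5 | +0.7 to +0.8 | 7.5 to 9% |
| Two of the four lost before session 15 | 0.8 | about +0.7 | 8% |
| Two of the four lost before session 15 | 0.5 | about +0.4 | 6.5% |
| VR high scorers leave instead | 0.8 | about −1.25 | 2% |
| Same rule in both arms | – | about 0 | about 5 to 6% |

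Ranges within a row are the spread between repeated simulation runs.

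**When there is a real effect.** Take a common rule with a steeper slope (log-odds 1.5 per SD), a true 30-session difference of 7.81 and a 15-session difference of 3.9 to 7.81. At correlations of 0.6 to 0.8 the completers' difference is too small by 0.4 to 1.1 points. A common rule is therefore harmless only when the arms do not differ at 15 sessions.

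**Using the 15-session score.** A likelihood estimate of the 30-session difference that conditions on the 15-session score has bias below 0.1 in the main case. Under random dropout its standard error is 2.86 against 3.04 at correlation 0.8, and 2.86/3.04 = 0.94, so 6% smaller. At 0.5 the gain is about 2%.

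**Its limit.** If VR dropout depends on the unseen 30-session score itself, the likelihood estimate keeps a bias of about +0.65 (correlation 0.8) to +1.2 (correlation 0.5).

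**The case against.** The strongest reply is that the article names tests and does not say that dropouts are excluded. Either test can be run on imputed data, intention-to-treat is stated, and handling of missing scores is commonly left to an analysis plan that is not shown. This stands. A reader might infer that section 2.11 describes a completers analysis under an intention-to-treat label; the text does not establish that. Nor does the step from 36 to 44 confirm it, because such inflation is routine whatever the analysis.

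A reader might also infer that any dropout linked to progress biases the comparison. It does not: with the same rule in both arms and no effect, the bias is about zero. Nothing in the article shows that the rule will differ by arm, and the direction could go against VR.

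The Introduction speaks of change in the measures. If the value tested is change from baseline, the baseline score enters by subtraction. Section 2.11 does not say so, and the 15-session score would remain unused at 30 sessions.

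Finally, a repeated-measures model is no complete cure. It does not remove bias from dropout that follows unobserved scores, and it gains nothing for patients lost before session 15.

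What remains is the choice of test, which the article does fix. One value per patient is a weak use of three assessments when a fifth of patients may leave.

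**Conclusion.** The point holds as an improvement to the analysis, not as a proven contradiction with intention-to-treat. As stated, the 30-session comparison uses neither the baseline nor the 15-session score, and the place of patients lost between the two visits is open.

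If completers alone are compared, the plausible size under VR-only, score-related dropout is a bias of about 0.8 to 1.2 BESTest points, against a limit of 7.81, and a one-sided type I error of about 9 to 11%. The lower end is soft, since repeated runs at correlation 0.5 gave 7.5 to 9%. These figures rest on SD 9.2, correlations of 0.5 to 0.8, four losses per arm all after session 15, and a log-odds of 1 per SD; none is in the article. The bias shrinks if some losses come earlier and changes sign if high scorers leave.

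**What to change.** For each continuous primary scale, make the primary analysis one linear mixed model for repeated measures on the 15- and 30-session scores. Include arm, visit, arm-by-visit, baseline score and baseline-by-visit, with unstructured covariance and Kenward–Roger degrees of freedom. Report the arm difference with its confidence interval at each visit.

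Keep the two-sample t-test or Mann–Whitney test as a sensitivity analysis. Add one sensitivity analysis for dropout that depends on unobserved scores and one for randomised patients with no post-baseline score, whom the model omits. State how each group of patients enters the intention-to-treat analysis.

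The cost is a change of wording and slightly more analysis work, with no extra data or patients. The model assumes that dropout is explained by observed scores. That is weaker than what a completers test needs, but it is still an assumption, hence the added sensitivity analyses.
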